### 3. Staff well-being

All CRT clinical staff will be asked to complete a self-report questionnaire at two time points: study baseline and 1-year follow-up. It will cover the demographic characteristics and the role of the CRT and will include the following:The Maslach Burnout Inventory [44]. This is a 22-item measure of staff morale, providing information about emotional exhaustion, cynicism, and perceived personal accomplishment. Its possible range is 0 to 132.The General Health Questionnaire [45]. This is a 12-item measure of general psychological health that yields a score ranging from 0 to 36.The Work-Related Acceptance and Action Questionnaire [46]. This is a seven-item scale of work-related psychological flexibility that yields a score ranging from 7 to 49.The Work Engagement Scale [47]. This is a nine-item measure of positive work engagement that yields a score ranging from 0 to 54.

### 4. Qualitative and process evaluation

#### Fidelity reviews

CRT model fidelity will be assessed in all teams at baseline and 1-year follow-up using the CORE CRT Fidelity Scale [37], a 39-item measure yielding a total score ranging from 39–95.

### Monthly process monitoring

Monthly process monitoring for each CRT in the intervention arm will identify the fidelity items targeted in the service improvement plans and categorise the CRT facilitators’ implementation activities using a typology developed by the EBP Program as prioritisation, leadership, workforce, workflow, or reinforcement [31] to describe the facilitators’ activities and explore how they may relate to changes in team fidelity during the project.

#### Qualitative interviews

Topic guides for local facilitator interviews and CRT manager interviews and staff focus groups will examine the participants’ experiences of the CRT service improvement intervention; most and least helpful parts of the intervention; barriers and facilitators to its implementation, including local contextual factors; and the perceived impact of the intervention implementation on the CRT service delivery and outcomes.

## Procedures

The 1-year study intervention period will be the same for all teams within each participating NHS Trust, defined as starting from the date when the Trust’s CRT facilitator starts in post. Outcome data from Trust patient records will be collected for a 6-month period 6–12 months following the intervention start date. Outcome interviews with service users and staff, and the end-of-study CRT fidelity review, will be conducted between months 10 and 12 of the trial-intervention period.

### 1) Service user experience

#### Screening and recruitment

Clinical staff in participating CRTs will be asked to screen and identify consecutively discharged potential service user participants who meet the study’s inclusion criteria. Eligible service users will be approached close to the point of discharge by clinical staff from the CRT that supports them, who will explain the study briefly and ask if they are willing to be contacted by a researcher. A study researcher will then contact potential participants to explain what the study involves, answer any questions, and send a written study information sheet [48]. The researcher will make contact again to check the participant has understood the information sheet and has continued capacity to consent. Consent to participate and completion of the questionnaire can be done in one of the following ways: at a face-to-face meeting, via post, over the telephone (consent will be audio-recorded and stored securely), or online via a link sent by researcher (using UCL’s secure “Opinio” system). A copy of the consent form is provided as Additional file 2.

The interview will take approximately 15 minutes to complete. This process will continue until 15 service users from each team have completed the questionnaire. Participating service users will be offered a gift of £10 in acknowledgement of their time, given as cash or as an e-voucher, according to the participant preference.

### 2) Service use

For baseline and study outcome data from patient records, a study researcher will contact the appropriate administrators or informatics team within each NHS Trust. The study researchers will provide a pro forma that specifies clearly the nature of the information and time periods for which data are required. Administrators will be asked to provide the required patient-level data in anonymised form.

### 3) Staff well-being

A study researcher will visit the CRT team to publicise the study and answer any questions the staff may have about their involvement. The study researcher will assign a study identification number to each staff member. A master document linking CRT staff names to ID numbers will be stored securely at the research study office. An email will then be sent to all CRT staff containing an invitation to participate in the study, a study information sheet, their individual ID number, and a link to the online structured questionnaire hosted on the UCL's secure network. Consent to participate in the study will be provided by staff through completing the questionnaire.

### 4) Qualitative and process evaluation

#### Qualitative interviews

At the end of the 12-month intervention, a study researcher will contact all local facilitators and the managers of the six case study CRTs directly to invite them to participate in an individual interview. Staff focus group participants will be identified initially through liaison with managers of case study CRTs. A study researcher will provide potential participants with written information about the study, and the focus group and will include information on how to contact the researchers with any questions about participating. Staff will be informed that participation is entirely voluntary. Written consent will be taken from participants before the focus groups begin. Focus groups will be facilitated by two researchers from the study team. Focus groups and individual interviews will be audio-recorded.

#### Process monitoring

All monthly monitoring data collected from progress update phone calls with local facilitators will be coded under the EBP implementation categories by a researcher each month. [31]. Usage of the online resource kit will be monitored using Google analytics.

In addition, phone calls will be made to control team managers at 6 and 12 months: any reported impact of the Service Improvement Programme on their own team’s practice and any other major service improvement initiatives affecting CRTs taking place within NHS Trusts will be recorded.

### Data management

Study researchers will develop and manage a secure database for all quantitative study data using SPSS software and will store electronic copies of focus group transcripts using Nvivo qualitative software [Nvivo9: http://www.qsrinternational.com/product ] on the secure IT network at University College London. The study team will follow advice from Priment, a UCL Clinical Trials Unit, regarding development and maintenance of the study database.

Staff data will be entered by staff themselves, via the secure UCL online questionnaire. Service user data will be entered either by participants themselves via the secure UCL online questionnaire, or by researchers after a phone or face-to-face interview, or receipt of a paper copy of the questionnaire. All data will be transferred to the trial SPSS databases by study researchers. The study Chief Investigator will act as custodian of the data.

### Study oversight

The study sponsors, the Camden and Islington NHS Foundation Trust, act as guarantors for the trial, including insurance and indemnity arrangements, and are responsible for overseeing and auditing trial conduct. The study is supported by the Priment Clinical Trials Unit at University College London. Management of the study is coordinated through a trial management group, consisting of the study chief investigator and trial manager, trial statisticians and health economist, senior investigators, and representatives of Priment. Any proposed changes to the trial protocol during the study will be agreed on by the trial management group and submitted for approval to the research ethics committee by the study team. Service user and staff participants providing outcomes data for the trial will all provide informed consent to take part, using ethically approved procedures. Independent advice to the study team and oversight of the study is provided by a trial steering committee, which is independent of the sponsor and will meet at least annually during the trial. The steering committee comprises senior academics, including a statistician and a health economist; clinicians with relevant experience in acute care and/or service improvement; and service user and carer representatives with expertise by experience. A data monitoring committee (DMC) is not planned for this team-level intervention, but the trial steering committee will advise if any role for a separate DMC is indicated during the trial. No interim analyses are planned, and no stopping criteria are pre-set. Any serious adverse events reported to the study team will be screened by the chair of the trial steering committee as an independent reviewer. Any adverse events assessed as study-related will be reported, with the trial steering committee chair’s recommendation, to the study sponsor and the research ethics committee. Annual study progress reports will be provided by the study team to the sponsor and the research ethics committee.

## Analysis

### 1) Service user experience

We will test the hypothesis that participant satisfaction with the crisis resolution team, measured by the client satisfaction questionnaire [38] is greater in the teams that have implemented the Service Improvement Programme than control teams. This will be analysed using a multivariate linear random effects model with a random effect for CRT (mixed model), controlling for the mean baseline client satisfaction questionnaire score by CRT. Experiences of continuity of care, measured using Continu-um [43], will also be compared between those receiving and those not receiving the intervention.

Second, we will explore, using random effects modelling with a random effect for CRT, the extent to which the team fidelity score can explain variations in individual satisfaction with care.

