**Methods/design:**

Twenty-five CRTs from eight NHS Trusts across England will be recruited to this cluster-randomised trial: 15 CRTs will be randomised to receive the service improvement programme over a 1-year period, and ten CRTs will not receive the programme. Data will be collected from 15 service users and all clinical staff from each participating CRT at baseline and at the end of the intervention. Service use data will be collected from the services’ electronic records systems for two 6-month periods: the period preceding and the period during months 7-12 of the intervention. The study’s primary outcome is service user satisfaction with CRT care, measured using a client satisfaction questionnaire. Secondary outcomes include the following: perceived continuity of care, hospital admission rates and bed use, rates of readmission to acute care following CRT support, staff morale, job satisfaction, and general health. The adherence of the services to a model of best practice will be assessed at baseline and follow-up. Outcomes will be compared between the intervention and control teams, adjusting for baseline differences and participant characteristics using linear random effects modelling. Qualitative investigations with participating CRT managers and staff and programme facilitators will explore the experiences of the service improvement programme.

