### Randomisation

The 25 teams will be randomised to either receive the Service Improvement Programme (n = 15) or the control (n = 10) after the baseline fidelity reviews have taken place for all participating teams within each NHS Trust. Randomisation of the CRTs will be stratified by the NHS Trust to ensure that within each Trust, some CRTs will receive the intervention and some will act as control teams, to address the potential confounding factor of Trusts’ macro-level management and service processes. Randomisation will be conducted by a Priment (a University College London Clinical Trials Unit) statistician who is independent of the study. Randomisations will be conducted for all participating teams within each NHS Trust at the same time, once baseline fidelity reviews have been completed at all sites within the Trust. The CORE trial has made no arrangements for blinding: both participating services and researchers will be aware of the team allocation status. Service user participants providing data for the trial’s primary outcome are not expected to be informed of their team allocation, and the NHS Informatics Teams providing anonymised patient service-use data will not be aware of the team allocation status.

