### Sample size

A sample size calculation for the primary outcome measure (service user satisfaction measured using the Client Satisfaction Questionnaire [38]) determined the size of the service user sample. A sample of 375 participants (225 from 15 CRTs that have implemented the service improvement intervention and 150 from ten CRTs that have not) will give 97 % power to detect half a standard deviation difference in mean satisfaction (3.5 points assuming a typical SD of 7.0), and 80 % power to detect a small difference of just over one-third of a standard deviation, allowing for moderately large within-team clustering (ICC = 0.05).

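### Randomisation is stratified by NHS Trust, but the stated primary CSQ-8 model has no Trust term; if Trusts differ, inference is somewhat conservative

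*Protocol article*

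**What the plan says.** The abstract gives the structure: "Twenty-five CRTs from eight NHS Trusts across England will be recruited to this cluster-randomised trial". The Randomisation section gives the allocation, "The 25 teams will be randomised to either receive the Service Improvement Programme (n = 15) or the control (n = 10"), and the stratification: "Randomisation of the CRTs will be stratified by the NHS Trust to ensure that within each Trust, some CRTs will receive the intervention", with other teams in the same Trust acting as controls. The stated reason is "to address the potential confounding factor of Trusts’ macro-level management and service processes".

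The Analysis section, under Service user experience, specifies the primary comparison as a "multivariate linear random effects model with a random effect for CRT (mixed model), controlling for the mean baseline client satisfaction questionnaire score by CRT". The abstract describes the adjustment as "adjusting for baseline differences and participant characteristics using linear random effects modelling". Neither statement includes Trust, and no other section adds it.

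The Sample size section allows for clustering at team level only (ICC 0.05) and gives no Trust-level component. The number of teams per Trust and the within-Trust allocation ratios are not stated.

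**The concern.** Stratifying makes the arms similar with respect to Trust, so it reduces the true variance of the arm comparison when Trusts differ. A model without Trust leaves the between-Trust variation in the team-level residual. It therefore reports a standard error that does not reflect the gain from stratification. Intervals become too wide, the test rejects less often than its nominal level, and some of the precision gained by the design is lost.

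Stratification would balance Trust exactly only if every Trust had the same allocation ratio. If the ratios differ, arm and Trust are weakly associated, and a model without Trust leaves that association in place. Trust also carries calendar time: under Procedures, the intervention year starts when each Trust's facilitator takes up the post.

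**Working it through.** **1. The plan's own power figure.** Inputs from the Sample size section: "225 from 15 CRTs that have implemented the service improvement intervention and 150 from ten CRTs that have not", which "will give 97 % power to detect half a standard deviation difference in mean satisfaction (3.5 points assuming a typical SD of 7.0"), and ICC 0.05. Two-sided alpha of 0.05 is assumed because none is stated.
- Design effect = 1 + (15 − 1) × 0.05 = 1.70.
- SE = 7.0 × √[1.70 × (1/225 + 1/150)] = 7.0 × 0.1374 = 0.962 points.
- Power at 3.5 points = Φ(3.5/0.962 − 1.96) = Φ(1.68) = 95.3%, against 97% stated.
- Difference detectable with 80% power = 2.80 × 0.1374 = 0.385 SD, consistent with the article's second power statement.

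The stated power is close enough that it is not part of this point.

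**2. Can the ratio be constant across Trusts?** A common ratio would have to be 15:10 = 3:2, so each Trust would need a multiple of five teams. Eight Trusts would need at least 8 × 5 = 40 teams, and there are 25. At most two Trusts can be at 3:2:
- Three Trusts of five use 15 teams (9:6). The other five Trusts then have 10 teams, two each, so 1:1 (5:5). The total is 14:11, not 15:10.
- Two Trusts of five (6:4), three Trusts of three at 2:1 (6:3) and three Trusts of two at 1:1 (3:3) give 15:10.
- A Trust of ten at 6:4 leaves 15 teams in seven Trusts. That forces six at 1:1 and one Trust of three, at best 2:1, and a total of at most 14 intervention teams.

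At least six Trusts therefore depart from 3:2.

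**3. How large is the arm-Trust association?** In three assumed layouts that each give 15:10, R² of arm on Trust was 0.02-0.10. At ICC 0.05, with 50-80% of the between-team variance lying between Trusts, the Trust-driven imbalance had an SD of 0.12-0.35 CSQ points before baseline adjustment. Against 3.5 points that is 0.12/3.5 = 3% to 0.35/3.5 = 10%. Averaged over random Trust effects there was no bias.

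**4. How much does the baseline covariate absorb?** The baseline team mean comes from 15 different service users. At ICC 0.05 its reliability is 15 × 0.05/1.70 = 0.44, so it removes stable Trust differences only in part.

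**5. Standard errors and type I error with the baseline covariate in the model.** Simulation of 25 teams with 15 users each, ICC 0.05 and an assumed baseline to follow-up correlation of 0.7 for Trust and team effects. The layout shown is four Trusts at 1:1, two at 2:1, one at 3:2 and one at 4:2. The tests are t tests, and SEs are in CSQ points.

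| Trust share of between-team variance | Model SE, no Trust | True SD | Ratio | Type I error, no Trust | Type I error, fixed Trust | Power at 3.5, no Trust | Power at 3.5, fixed Trust |
|---|---|---|---|---|---|---|---|
| 0 | 0.933 | 0.944 | 0.99 | 5.2% | 5.0% | 94.8% | 92.4% |
| 50% | 0.925 | 0.864 | 1.07 | 3.3% | 5.1% | 96.2% | 96.4% |
| 80% | 0.911 | 0.805 | 1.13 | 3.0% | 4.8% | 97.4% | 98.2% |

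Across the three layouts at shares of 50-80%, the SE is 5-14% too large and type I error is 3.0-4.4%.

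**6. Power at 0.4 SD (2.8 points).** Fixed Trust effects gain 0-1 points at a 50% share and 2-3 points at 75%. They lose 4-5 points if Trusts do not differ.

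**The case against.** The strongest reply is that this is a modest efficiency point that depends on an unknown. The article gives no Trust-level variance. If that variance is zero, the stated model has correct standard errors and fixed Trust effects only lose power. The baseline team mean already absorbs part of any stable Trust difference; a calculation that leaves it out overstates the loss. The article is also a condensed account: its abstract mentions participant characteristics that the Analysis section does not list, and the analysis plan is not shown. All of this stands, and it limits the size of the point. It does not remove the mismatch, because the article names both the random effect and the covariate of its primary model and Trust is neither.

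A reader might infer more than the document supports:
- **That false positives are inflated.** Omitting a stratifier makes the test conservative.
- **That Trust differences or Trust-specific start dates bias the effect.** Every Trust contains both arms, and all teams in a Trust share one intervention period. These differences enter only through the small chance imbalance in step 3 of the working.
- **That p-values are too small because a normal reference is used with 25 teams.** The article states no reference distribution, estimation method or degrees of freedom. Such detail commonly belongs in the analysis plan.
- **That every other between-arm model has the same fault.** The Service use section names Poisson random effects modelling without listing the effects, and the Staff well-being section names no model.

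**Conclusion.** The point holds for the primary CSQ-8 model. The design treats Trust as important enough to stratify on, the stated model leaves it out, and the within-Trust ratios cannot be equal. If Trusts differ, the consequence is conservative inference. At ICC 0.05, with half to three-quarters of it between Trusts and a baseline to follow-up correlation of 0.7, SEs are about 6-13% too wide and type I error is about 3-3.5%. If Trusts do not differ, the SEs are correct. The Trust share, the correlation and the Trust sizes are assumptions, since the document gives none of them. The trial's validity is not threatened and the stated power is not in error. The wording should be corrected so that the analysis follows the randomisation.

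**What to change.** Add NHS Trust to the primary CSQ-8 model and name it in advance. The preferred form is a random intercept for Trust above the random effect for CRT, keeping the CRT mean baseline score as covariate.

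This is a change of wording and needs no new data. A random intercept costs little power if Trust variance is near zero. Fixed Trust effects are a legitimate alternative, but they use seven degrees of freedom (8 − 1) out of 25 teams and would cost about 4-5 points of power at 0.4 SD if Trusts do not differ. The choice between the two should therefore be made before outcome data are seen.

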### 2) Service use

We will use routine data to compare service use patterns between teams that have received the Service Improvement Programme and the control teams. Data on admission rate, bed use, and population size will be measured over 6-month periods before and after intervention introduction. We will also explore whether there is any evidence of differences between intervention and control areas in extent of change in rates of compulsory detention under the Mental Health Act and of readmissions within 6 months of an initial admission to acute care. Other routinely collected indicators of CRT functioning, such as referral sources and caseload composition will also be examined. Data will be analysed using Poisson random effects modelling. Either bed use or admission rate will be set as the exposure variable as appropriate.

If differences between the two groups are found, national reference costs will be applied to resource use (admission, bed days and re admissions) to calculate the cost difference between resource kit implementation and control areas. A difference in difference model will be used, looking at before and after effects in the two areas using the most appropriate statistical model as determined by Akaike information criteria (AIC) and Bayesian information criteria (BIC) values. This is likely to be a general linear model with log link and family gamma. The model will take the same form as the Poisson model above.

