Despite indications of the potential effectiveness of CRTs, considerable reservations have emerged about their delivery in routine settings in the UK, most notably in recent reports by Mind [14], the Schizophrenia Commission [15], and the Care Quality Commission [16]. Both CRT and ward managers still view a significant minority of hospital admissions as unnecessary [17]. The impact on bed use appears to vary considerably between areas [11, 18, 19], and the reductions in bed days tend to be less marked than those in admissions [9, 11]. Rates of compulsory admissions have continued to rise in England since 2000 despite the national implementation of CRTs [18–20], and a recent national audit raised concerns about the number of suicides by service users receiving CRT care [21]. Service users and carers, whilst mainly positive about receiving care in their own homes, report important areas of dissatisfaction with CRTs [14, 22, 23], especially regarding the continuity of care, the quality of relationships with staff, and a narrow range of support on offer, which sometimes focuses principally on medication and short-term symptom control.

The UK experience, and similar challenges in Norway, where CRTs are also mandated at the national level but with variable implementation [24], illustrates that the national mandate, policy, and guidelines have been insufficient to ensure consistent and complete implementation of this complex intervention. A survey of CRTs in 2005/6 [25] and another in 2011/12 [26] confirmed considerable variation in CRT resources, organisation, and service delivery. One potential reason for inconsistencies in CRT implementation is that the CRT model and its theoretical basis were not highly specified at the outset [4, 26], nor has a means of measuring fidelity to a model of good practice been developed and disseminated. Improving acute mental health services is a current UK policy priority [27], yet available quality improvement resources are lacking for CRTs to promote best practice.

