### 2) Service use

Anonymised service data for two cohorts of service users will be collected at two time points – baseline and follow-up: (1) a cohort of all service users admitted to the CRT during a 1-month period ending 6 months prior to the study baseline date and another cohort of all service users admitted during month 7 of the study intervention period at each Trust and (2) all service users admitted to the acute inpatient services during a 6-month period up to the study baseline date and during months 7–12 of the study intervention period at each Trust.

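### The Poisson service-use models name two outcomes, bed use and admission rate, as the only candidate exposures and omit population size, so a real fall in bed use could vanish or appear as a rise

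*Protocol article*

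**What the plan says.** The Analysis section, under 2) Service use, gives the model, "Data will be analysed using Poisson random effects modelling", and then the exposure: "Either bed use or admission rate will be set as the exposure variable as appropriate". The same paragraph lists the data: "Data on admission rate, bed use, and population size will be measured over 6-month periods before and after intervention introduction". It also plans to explore "rates of compulsory detention under the Mental Health Act and of readmissions within 6 months of an initial admission to acute care".

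The Abstract (Methods/design) counts among the secondary outcomes "hospital admission rates and bed use, rates of readmission to acute care following CRT support". The Background says of earlier CRT evidence that "the reductions in bed days tend to be less marked than those in admissions".

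A cost analysis follows only if the arms differ. It is a difference-in-difference model, and the protocol says that it shares the form of the Poisson model. The section does not say which exposure belongs to which outcome, at what level the random effect sits, or whether baseline enters as a data row or as a covariate.

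On cohort 1 follow-up, Sample, 2) Service use, defines the outcome sample as "another cohort of all service users admitted during month 7 of the study intervention period at each Trust". Measures, 2. Service use, promises six months of follow-up for each cohort 1 sample and places the second one in months 6–7. Procedures says "Outcome data from Trust patient records will be collected for a 6-month period 6–12 months following the intervention start date".

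**The concern.** The exposure of a count model is the amount at risk: people, or people × time. Its log enters with a fixed coefficient of one, so the model describes the outcome per unit of exposure. If the exposure is itself something that the intervention changes, the arm effect is no longer the effect on the outcome. It becomes the effect on a ratio of two post-randomisation quantities.

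The two named exposures are exactly the quantities that the programme is meant to reduce. Bed use with admissions as exposure becomes days per admission. Admissions with bed use as exposure become admissions per bed day. Neither answers the question in the Aims, which is whether acute service use falls. The cost analysis depends on whether these comparisons show a difference, so an effect that is hidden or reversed here carries over to it.

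**Working it through.** The service-use section states no figure to reproduce. The effect sizes, counts and variances below are assumptions. Admission rate is read as the number of admissions in the same six months.

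**1. What the model estimates.** With log(admissions) as offset, log E[bed days] = log(admissions) + β·arm + other terms. Ignoring the weighting introduced by the random effect, exp(β) = RR(bed days) / RR(admissions).

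| Assumed RR, admissions | Assumed RR, bed days | Bed use with admissions as exposure | Admissions with bed use as exposure |
|---|---|---|---|
| 0.80 | 0.90 | 0.90/0.80 = 1.125 | 0.80/0.90 = 0.889 |
| 0.90 | 0.95 | 1.056 | 0.947 |
| 0.70 | 0.85 | 1.214 | 0.824 |
| 0.80 | 0.80 | 1.000 | 1.000 |
| 0.90 | 1.00 | 1.111 | 0.900 |

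With population as exposure, the first row is estimated as 0.80 and 0.90. The sign for bed use reverses whenever both fall and bed days fall less than admissions, which is the pattern that the Background reports.

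An example in counts: admissions fall from 100 to 80, mean stay is 30 days, and the averted stays average 10 days. Bed days go from 3000 to 3000 − 20 × 10 = 2800, a fall of 6.7%. Days per admission go from 30 to 2800/80 = 35, a rise of 16.7%.

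**2. Standard errors, by layout.** A Poisson random-intercept model was simulated with 15 against 10 teams, no true effect, a correct population offset and 150 runs per setting. The between-team SD was 0.3 on the log scale. Mean count per team-period was 150 (admissions) or 3000 (bed days), and team-by-period SD was 0.1 or 0.2.

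| Mean count | Team-by-period SD | Before/after rows: true SD / model SE | Type I error | Follow-up row only, baseline as covariate: true SD / model SE |
|---|---|---|---|---|
| 150 | 0.1 | 0.074/0.045 = 1.6 | 25% | 1.14 |
| 150 | 0.2 | 0.129/0.045 = 2.9 | 47% | 1.01 |
| 3000 | 0.1 | 0.058/0.010 = 5.7 | 73% | 1.00 |
| 3000 | 0.2 | 0.128/0.010 = 12.8 | 82% | 1.05 |

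(Ratios are taken before rounding.) A closed form agrees for the before/after layout. For mean count μ and team-by-period SD σ, the ratio is about √(1 + μσ²): √2.5 = 1.6, √7 = 2.6, √31 = 5.6 and √121 = 11. In the follow-up-only layout, type I error was 5% to 9%; at 9% the Monte Carlo error is √(0.09 × 0.91/150) = 2.3 points.

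Bed days also arrive in whole stays. Even with no team-by-period variation, their variance-to-mean ratio is mean stay × (1 + CV²). Mean 20 and CV 1 give √40 = 6.3 as the SE factor in the before/after layout. Mean 30 and SD 35 give √(30 × 2.36) = 8.4.

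**3. Cohort 1 follow-up.** Month 7 runs from 6 to 7 months after the start. With records to 12 months, follow-up is 12 − 7 = 5 to 12 − 6 = 6 months, on average 5.5 if admissions are evenly spread. Against the stated 6 months, that is 0.5/6 = 8% short. The baseline sample was admitted in a month ending six months before baseline, so all of it has the full 6 months.

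**The case against.** **The wording leaves room.** The exposure is to be chosen as appropriate, and the sentence follows a list of several outcomes. Admissions are a proper denominator for readmission after an initial admission, or for the share of admissions that are compulsory. Population size is collected in the same paragraph, most naturally as a denominator. This stands in part. The text does not state that bed use will be modelled over admissions, so sign reversal is a risk of the wording and not a stated analysis. But the sentence offers only two exposures, neither is population, and it covers all the service-use data. If exposure was a slip for outcome, the text still needs correcting.

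**The model already allows for variation beyond Poisson.** This stands. A team random effect is such a term, and with one follow-up row per team the standard errors were about right. Difference-in-difference is named only for the cost model, and the Abstract speaks of adjusting for baseline differences. The shared-form statement makes a before/after layout plausible but does not fix it. How remaining overdispersion is handled is also commonly left to an analysis plan, which is not at hand.

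**Cohort 1 has a stated six-month follow-up.** It does, in Measures. That is why the matter is a conflict between sections and not a settled shorter follow-up. The shortfall applies to both arms, so it mainly disturbs before/after levels.

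**Conclusion.** The exposure point holds. The protocol names two outcomes as the candidate exposures and leaves out the population denominator that it collects. For bed use over admissions, the estimate is the bed-day ratio divided by the admission ratio. The algebra needs no assumption; the sizes (1.125 at assumed ratios of 0.80 and 0.90, and 1.00 for equal falls) depend on the assumed effects.

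Three stronger readings are not supported. A reader might infer that the model ignores extra-Poisson variation, so that bed-day p-values are unusable. That would follow only in a before/after layout with a team intercept alone, which the text suggests but does not fix, and the sizes rest on counts and variances that the protocol does not give. A reader might infer that the bed-use result will point the wrong way; the text permits this but does not prescribe it. A reader might put the cohort 1 shortfall at 15% by setting 5.5 months against 6.5; Measures sets baseline follow-up at six months, so 8% is the supportable figure.

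These are secondary outcomes, and satisfaction is analysed with a separate linear mixed model. The point should be fixed before analysis but is not critical to the trial.

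**What to change.** - **Exposure.** State that catchment population × time is the exposure for admissions and for bed days. Keep admissions as a denominator only for outcomes defined per admission, such as readmission or the compulsory share. Length of stay may be reported, labelled as such. This changes wording only, since population size is already to be collected.
- **Layout and variance.** State whether baseline is a data row or a covariate. If before and after rows are used, add a team-by-period random effect, or use a negative binomial model with cluster-robust standard errors, or analyse team-level changes in log rate. The cost is wider intervals, which in that layout are the correct ones.
- **Cohort 1.** Reconcile the Sample, Measures and Procedures sections on the admission month and the end of records. Then truncate both samples at the same length of follow-up or use person-time as exposure. Either can be done in the analysis. Extending the records or moving the admission month would also equalise follow-up, but would change the data request to the Trusts.
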